### Eligibility criteria

Two groups of participants will be approached.

The first group will belong to the general population and will be screened with the NL-IHRS. These people will be over 18 years of age and work or live in the COB.

The second group will be composed of people at moderate cardiovascular risk, according to the NL-IHRS (range 9 to 15) and will be recruited for the behavioural change intervention. The research team will only focus on people at intermediate cardiovascular risk because interfering with the habits of healthy people could worsen their existing behaviour. Another consideration is that the provision of exclusive non-pharmaceutical intervention for people at high cardiovascular risk is at odds with current French cardiovascular recommendations.

Non-inclusion criteria for the people undergoing the screening are: aged under 18, current pregnancy, living and working outside COB, personal history of cardiovascular disease.

Non-inclusion criteria for participants undergoing the RCT are: low cardiovascular risk according to the NL-IHRS (score strictly under 9), high cardiovascular risk according to the NL-IHRS (score strictly over 15).

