#### Outcomes

The primary outcome will be the comparison of the NL-IHRS between the two branches of the study after 24 months.

The secondary outcomes after 24 months will be quality of life, as assessed by the WHOQOL-BREF [17], modification of diet, according to the DASH questionnaire [18], modification of physical activity, following the IPAQ-short [19], BMI reduction, smoking level, modification of self-declared alcohol consumption.
The WHOQOL-BREF questionnaire was derived from the WHOQOL-100 in 1996 to assess quality of life by using thirty-three questions within the four following domains: physical health, psychological domain, social relationships and environment.The DASH questionnaire was created in 2016 to assess, by means of eleven questions, the quality of an individual’s diet, according to the Dietary Approach to Stop Hypertension. This diet was designed along the lines of the Mediterranean diet to improve the cardiovascular risk profile of the consumers [20].The IPAQ was created in 2003 to assess physical activity. The short version comprises seven questions in four blocks which describe intense activity, moderate activity, walking in the last 7 days and time spent seated. The score of the IPAQ-short can be converted in Metabolic Equivalents of Task, a standardised measurement of physical activity level.

The tertiary outcomes will be the same as previously stated, assessed at 6 and 12 months. The implementation strategy will be assessed by mixed methods comprising qualitative research methods and quantitative descriptive epidemiological studies [21]. Quantitative implementation data collected at 12 and 24 months will consist of the number of people screened with the NL-IHRS, the number of people entering the behavioural change intervention, the number of people completing the entire intervention, the cost of the intervention. Qualitative studies will be constructed using the Re-Aim model [22], exploring invention barriers and facilitators and perspectives from screeners, community champions, stakeholders and members of the research team.

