### Statistical methods

For stage 1, a descriptive epidemiological analysis will be carried out on the screened population. The total number of screenings, the distribution of the population within low-, intermediate- and high-cardiovascular risk scores, and the frequency of the modifiable risk factors listed in the score will be described.

For stage 2, the calculation of the number of subjects required is based on the comparison of the mean NL-IHRS between the two branches of the study: for a power of 80%, an alpha risk = 0.05 and an effect size (mean difference / standard deviation) of 0.20, the number of subjects required is 394 per branch. The figure of 985 subjects, including about 20% potentially lost to follow-up, should be included in the total. With the number of subjects being 394 patients per branch and the hypothesis of an effect size of 0.20 for each secondary endpoint, the test power is approximately 68% for each secondary endpoint using the Holm-Bonferroni correction to allow for multiple comparisons.

The analysis of the RCT will be conducted on an “intention to treat” basis.

No intermediate analysis will be conducted because this study leads to no biomedical risk.

A hierarchical analysis will be conducted in two steps. First, a comparison of the mean NL-IHRS between the two branches at alpha risk = 0.05 then, in the event of a statistically significant result, a comparison of the 6 secondary endpoints between the two branches, using the Holm-Bonferroni correction to consider the multiple comparisons made at this stage. In accordance with the principles of hierarchical analysis, the tests provided for in the second step will only be carried out in a demonstrative manner if the test performed in the first step is statistically significant (*p* < 0.05).

The quantitative outcomes will be compared between the two branches using a Student test. The qualitative endpoints will be compared between the two groups using a Chi-square test. Secondary, multivariate analyses will be performed using a linear model to adjust for potential confounding factors.

Missing data will be identified via the electronic CRF, and investigators will be called back to complete the data. The remaining incomplete files will be declared as lost to follow-up.

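### The primary test of 24-month NL-IHRS is an unadjusted Student test, although a pre-randomisation NL-IHRS exists for every participant: a valid test that gives up precision

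*Protocol article*

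**What the plan says.** The protocol article's Outcomes section defines the endpoint: "The primary outcome will be the comparison of the NL-IHRS between the two branches of the study after 24 months". Statistical methods places it first in the hierarchy, "First, a comparison of the mean NL-IHRS between the two branches at alpha risk = 0.05", ahead of six secondary endpoints that are tested confirmatorily only if it succeeds. The same section fixes the method: "The quantitative outcomes will be compared between the two branches using a Student test". The only covariate model comes next: "Secondary, multivariate analyses will be performed using a linear model to adjust for potential confounding factors". Baseline NL-IHRS is not named there.

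Eligibility criteria limits the RCT to NL-IHRS scores from 9 to 15 and excludes anyone below or above. Stage 1 describes how screeners score each person on a tablet. Stage 2 describes contact and randomisation after that stage is complete.

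The sample size is computed "for a power of 80%, an alpha risk = 0.05 and an effect size (mean difference / standard deviation) of 0.20", and "the number of subjects required is 394 per branch". The total is 985 with about 20% loss to follow-up.

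**The concern.** The value of the primary outcome before randomisation is usually among the best predictors of its later value, and here it is held for everyone at no extra cost. The plan makes no use of it in the test that decides the trial. Adjusting for it targets the same difference in means with a smaller standard error.

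The planned power is only 80% for a small effect, and the primary test is the gate to all six secondary endpoints. A missed true effect would therefore also remove every confirmatory secondary claim. The method is written into the protocol, so an analysis plan that is not shown would have to change this choice rather than fill a gap.

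**Working it through.** **Inputs from the protocol (Statistical methods):** alpha 0.05, power 80%, effect size d = 0.20 SD, 394 per arm, about 20% loss, 985 in total. Allocation is equal (Abstract).

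**Input not in the protocol:** r, the correlation between baseline and 24-month NL-IHRS within arm. Assumed range: 0.2 to 0.5.

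**Step 1: reproduce the plan's figure.** For an unadjusted two-sided comparison of means, n per arm = 2(1.96 + 0.842)² / 0.20² = 393 by the normal approximation. The exact t calculation gives power of 79.96% at 393 and 80.06% at 394, so 394 is correct. A one-sided test would need 310, so the plan is two-sided. For loss, 2 × 394 / 0.80 = 985. The design therefore takes no credit for the baseline score.

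**Step 2: effect of adjustment.** With baseline as a covariate, the residual variance is multiplied by (1 − r²). The cost is one degree of freedom, which is negligible with 788 analysed. The standardised signal at 394 per arm is 0.20 × √(394/2) = 2.807, so power = Φ(2.807 / √(1 − r²) − 1.96). The n for 80% power is the Step 1 formula times (1 − r²), rounded up.

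| r | Variance reduction | Power at 394 per arm | n per arm for 80% power | Total with 20% loss |
|---|---|---|---|---|
| 0 | 0% | 80.2% | 393 | 983 |
| 0.2 | 4% | 81.7% | 377 | 943 |
| 0.3 | 9% | 83.7% | 358 | 895 |
| 0.4 | 16% | 86.5% | 330 | 825 |
| 0.5 | 25% | 90.0% | 295 | 738 |

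**Step 3: why r is not taken higher.** Restricting entry to 9 to 15 narrows the baseline spread. If scores were uniform over those integers, their SD would be √((7² − 1)/12) = 2.0. As an illustration, assume an SD of 5 to 7 and a correlation ρ of 0.5 to 0.8 in the unrestricted population. With u = 2.0 / SD, the correlation in the trial is ρu / √(1 − ρ² + ρ²u²):

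- SD 7, ρ 0.5: r = 0.16, a variance reduction of about 3% and power of about 81%.
- SD 5, ρ 0.8: r = 0.47, a variance reduction of about 22% and power of about 89%.

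**Step 4: a change score is not a substitute.** With equal variances, its variance relative to the 24-month score is 2(1 − r). That is 1.4 at r = 0.3 and reaches 1.0 only at r = 0.5. Below that, a change score loses precision, whereas covariate adjustment does not do so materially.

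**The case against.** The strongest reply is that nothing is wrong. Under randomisation the unadjusted comparison of means is unbiased, it is the test for which the trial was sized, and omitting baseline does not take power below the planned 80%. That stands, and it is why the point concerns efficiency. It does not answer why a gain that needs no new data should be left unused in the primary test.

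The size of the gain is also open to challenge, because the protocol gives no r. Besides the range restriction, participants are randomised only after screening ends, so for those screened early the interval to the final score exceeds 24 months, which tends to lower r further. At r = 0.2 the gain is between one and two percentage points. This stands too. Power figures based on r = 0.6 or more should not be quoted.

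Chance imbalance in baseline adds little to the argument. With a baseline SD of 2 and 394 per arm, the standard error of the baseline difference is 2 × √(2/394), or about 0.14 points.

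Three stronger readings are tempting but not supported:

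- **That adjustment would repay the power lost to group sessions.** This needs both r and an intracluster correlation (ICC), and the protocol gives neither. Suppose only the intervention arm is clustered, in groups of m = 10 to 15 (Stage 2: RCT). The average variance inflation is then (1 + [1 + (m − 1)ICC]) / 2, and the break-even r is √(1 − 1/inflation). At an assumed ICC of 0.01, inflation is 1.045 to 1.07 and r must be 0.21 to 0.26. At 0.05, inflation is 1.225 to 1.35 and r must be 0.43 to 0.51. The offset may be full, partial or slight.
- **That the secondary adjusted models are a fault.** They are labelled secondary, and listing their covariates is commonly left to an analysis plan. They do not touch the alpha = 0.05 test.
- **That baseline already enters the primary outcome.** Aim of the study speaks of a 15% decrease in the score, which could suggest change from baseline. However, Outcomes, Sample size and Statistical methods all describe a comparison of the score between arms at 24 months.

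**Conclusion.** The point holds as an avoidable loss of precision in the primary analysis. The planned test is valid and agrees with the sample size of 394 per arm. For an assumed r of 0.2 to 0.5, adjusting for baseline NL-IHRS would lower the residual variance by 4% to 25% and raise power at d = 0.20 from 80% to about 82% to 90%. The lower and middle parts of that range are the more plausible, given the restricted entry scores. The reading of the protocol is certain; the size of the benefit depends on a correlation that the protocol does not state. A reader might infer that the trial is underpowered or its primary result biased because baseline is left out. The documents do not support either inference.

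**What to change.** In Statistical methods, define the alpha = 0.05 primary test as a linear model of 24-month NL-IHRS on arm, with the pre-randomisation NL-IHRS as a prespecified continuous covariate. Report the adjusted mean difference with its confidence interval, and keep the Student test as a sensitivity analysis. Use the same model for quantitative secondary endpoints wherever a baseline value is collected. Outcomes words several of these as modification or reduction, so state for each whether the response is the 24-month value or the change, with baseline as covariate in either case. The secondary confounder-adjusted models may stay.

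The sample size need not change: 394 per arm remains adequate by the plan's own assumptions, and any gain in precision is a margin. The cost is one or two sentences, made before outcome data are examined, with no new data and no added burden on participants.

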**Methods:**

A two-step RCT hybrid type 1 implementation study will first of all screen a population using the Non-Laboratory INTERHEART Score (NL-IHRS) and will involve health-care students at public events in the COB area until 1000 participants have been recruited. Second, a RCT will be carried out. The research team will contact each participant with an intermediate NL-IHRS in order to include them. Participants will be over 18 years of age and work or live in the COB area. Participants will be equally randomised in two groups. The intervention group will receive brief advice plus behavioural change guidance carried out by community champions. The control group will receive brief advice only. The main objective for the RCT is to assess a difference of at least 15% in the NL-IHRS between the two groups after 24 months. The primary outcome will be analysed with intention to treat. Secondary outcomes for the RCT will be assessed using validated questionnaires: the WHOQOL-BREF, the DASH Q questionnaire, the IPAQ-short; smoking level will be assessed according to the NL-IHRS scoring system; a modified self-declared alcohol consumption questionnaire has been developed and gauges will be used to assess BMI. The implementation strategy will use mixed methods: qualitative research methods and quantitative epidemiological studies.

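### The 68% power claimed for each secondary endpoint holds only for 1-df comparisons; an ordered smoking or alcohol endpoint with three or more levels would fall short under the planned Chi-square test

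*Protocol article*

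**What the plan says.** The Statistical methods section of the protocol article sets two general rules. Quantitative outcomes get a Student test. For the rest, "The qualitative endpoints will be compared between the two groups using a Chi-square test". No trend, rank or ordinal test is named.

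The same section sizes the trial "for a power of 80%, an alpha risk = 0.05 and an effect size (mean difference / standard deviation) of 0.20" and concludes that "the number of subjects required is 394 per branch". It then carries the effect size over to the second step of the hierarchy: under "the hypothesis of an effect size of 0.20 for each secondary endpoint, the test power is approximately 68% for each secondary endpoint", with Holm-Bonferroni correction over six endpoints. The ratio of mean difference to standard deviation is the only definition of effect size given.

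Smoking is described in three ways. In the abstract, "smoking level will be assessed according to the NL-IHRS scoring system". The Outcomes section lists it as a level. The Sample size section lists it as a reported status. Self-declared alcohol consumption is also a secondary outcome, with no scale given. The article does not say how many categories either has, or which of the two tests applies to each.

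**The concern.** Four of the six secondary endpoints (WHOQOL-BREF, DASH, IPAQ-short and BMI) are scores or measurements and fall naturally under the Student test. Smoking and alcohol are the natural candidates for the Chi-square rule. A level taken from a risk-scoring system is ordered, and the trial's question is directional: do participants smoke less when champions are added to brief advice?

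A Pearson Chi-square test on k levels does not use that order. It asks whether the two distributions differ in any way, on k − 1 degrees of freedom. Two things follow when k is 3 or more:

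- A genuine downward shift is more likely to be missed than the stated power suggests, because the power figure belongs to a comparison of two means.
- A significant result does not by itself show a reduction, since a rearrangement of levels with no net reduction can also reject. Second-step tests count as demonstrative once the primary succeeds, so such a result could be reported as confirmatory.

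**Working it through.** **Inputs.** From Statistical methods: 394 per arm, effect size 0.20, alpha 0.05 (sidedness not stated; two-sided reproduces the figures), six secondary endpoints, Holm-Bonferroni. From the abstract: 1:1 allocation. Assumed, because the article does not give it: the number of levels k.

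**Step 1: reproduce the sample size.** Normal approximation: n = 2 × (1.960 + 0.842)² / 0.20² = 392.4, so 393 per arm. The t-based calculation gives 393.4, so 394. With 20% loss, 2 × 394 / 0.80 = 985. Both stated figures reproduce.

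**Step 2: reproduce the 68%.** Each 1-df test has mean 0.20 × √(394/2) = 2.807 on the z scale. Holm was simulated on six two-sided tests, all with a true effect of 0.20 (400,000 replicates):

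| Correlation between endpoints | Power per endpoint |
|---|---|
| 0 | 68.6% |
| 0.2 | 68.0% |
| 0.5 | 67.1% |
| 0.7 | 66.3% |

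Plain Bonferroni at 0.05/6 = 0.00833 gives 56.7%. So the stated figure is the Holm power with all six effects true and every test on 1 df. It is calculated correctly for that case.

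**Step 3: replace one test by a Chi-square on k levels.** The noncentrality is kept at 2.807² = 394 × 0.20² / 2 = 7.88, and only the degrees of freedom change, to k − 1. Holm is run with the other five endpoints on 1 df, all independent:

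| Levels (assumed) | df | Power at 0.05 | Power at 0.05/6 | Power under Holm |
|---|---|---|---|---|
| 2 | 1 | 80% | 57% | 68.5% |
| 3 | 2 | 71% | 46% | 58% |
| 4 | 3 | 65% | 39% | 51% |
| 5 | 4 | 60% | 34% | 46% |

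The loss under Holm is about 10 points with 3 levels, 18 with 4 and 23 with 5.

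**Step 4: is the noncentrality fair?** A true ordered shift of 0.20 SD on the score scale need not give exactly 7.88. Proportional-odds shifts calibrated to 0.20 SD, with assumed category distributions of 3 to 5 levels, give noncentralities of 7.9 to 8.9 and Chi-square power of 40% to 46% at 0.05/6, against 56.7% for the 1-df test. The loss is slightly smaller at 4 and 5 levels but remains.

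**Step 5: ordered against unordered test on the same data.** Five levels, assumed control probabilities 0.45, 0.25, 0.10, 0.10 and 0.10, cumulative log-odds shift 0.40 (about 0.20 SD on the score scale), 20,000 runs. Power was 66% for Chi-square against 85% for Wilcoxon at alpha 0.05, and 40% against 64% at 0.05/6.

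**Step 6: readings with no loss.** For a two-level status with a Cohen h of 0.20, power at 0.05/6 is about 56%, essentially the 1-df figure of 56.7%. A Student test on a numerical smoking score is the 1-df case itself.

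**The case against.** The strongest objection is that nothing in the article sends smoking to the Chi-square test. The abstract describes it as assessed by a scoring system, which suits a Student test. The Sample size section introduces its list of secondary outcomes as differences in scores. The power statement applies a mean-difference effect size to all six endpoints, which can be read as a plan to compare six means. If smoking is instead a two-level status, Chi-square has 1 df. On either of these readings nothing is lost. This objection stands, and it is why the point is conditional.

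A reader might infer something stronger: that the 68% is wrong, or that the plan is known to deliver less for smoking. The documents do not support this. The 68% reproduces, and neither the test for smoking nor its number of levels is fixed.

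It can also be said that coding a secondary endpoint is commonly left to the analysis plan, that a Chi-square test is valid and controls type I error, and that direction can be read from the reported proportions. That the levels are not counted is indeed no finding. But the article does fix a test for qualitative endpoints and does promise one power for every secondary endpoint, and these two statements do not fit together for an ordered endpoint with three or more levels.

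A last objection is that the simulated shift in step 5 exceeds 0.20 SD, because Wilcoxon reaches 85% where 80% would be expected. It does not hold to any material degree: the shift is about 0.20 SD on the score scale. The 80% is the power of a comparison of means, and a rank test can do better against a proportional-odds shift.

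**Conclusion.** The concern holds conditionally. The claim of about 68% for each secondary endpoint is right for 1-df comparisons. It does not carry over to an unordered Chi-square test on three or more ordered levels, where power under Holm is about 58% (3 levels), 51% (4) or 46% (5). These figures assume the number of levels, 394 analysed per arm, a shift worth 0.20 SD, a true effect of 0.20 on the other five endpoints, and independence between endpoints. With a two-level status or a Student test on the score, the shortfall is zero.

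Severity is minor. At stake is one secondary endpoint, or two if alcohol is recorded in ordered classes, tested confirmatorily only after a significant primary result. The primary comparison, the sample size and the type I error rate are unaffected.

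**What to change.** In Statistical methods:

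- State the scale on which smoking and alcohol will be analysed.
- Analyse any ordered categorical secondary endpoint with a 1-df ordered test: Wilcoxon rank-sum with ties, a trend test, or a proportional-odds model, which also gives an odds ratio for a lower level.
- Keep Chi-square for two-level or unordered endpoints.
- State that the 68% applies to 1-df comparisons.

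The cost is wording only: same data, same visits, same sample size. The one statistical downside is that an ordered test is less sensitive to a non-monotone change, such as movement from both ends towards the middle, which is not what the trial asks about. The change should be made before unblinded data are seen.

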In the field, screeners will canvass participants, assess the NL-IHRS and deliver the appropriate brief advice. When they have screened someone at intermediate cardiovascular risk, they will offer the participant inclusion in the second stage. Participants willing to be included will give their name, phone number, e-mail address and postal address in a separate sheet, collected by the junior researchers. Participants at low risk will be given the brief advice and positive reinforcement. Participants at high risk will be given the brief advice and be strongly recommended to get an appointment with their usual physician. Screeners will be supported in the field by the junior researchers who will refer to the research team if there is a problem.

Implementation in this stage will include quantitative evaluation, described in the statistical analysis chapter. Qualitative implementation will focus on barriers and facilitators related to screening, as perceived by the screeners, conducted using either focus-groups or individual interviews. A purposive sample of screeners will be created. The sampling criteria will include age, number of participants screened and location of the screening. Data collection will continue until theoretical saturation of the data is reached. A thematic analysis will be performed. Two researchers, working blind, will code the data then merge their analyses.

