#### Sample size

The primary outcome will be analysed with intention-to-treat. An inter-group comparative analysis will be performed at the end of the intervention on the primary outcome. A difference in the mean NL-IHRS of 15% is expected between the intervention and the control groups. Secondary outcomes at 24 months will consist of differences in scores for quality of life (WHOQUOL-BREF), DASH questionnaire, IPAQ-short, reported smoking status, reported alcohol consumption. Tertiary outcomes, at 6- and 12-months, will consist of differences in the NL-IHRS, WHOQUOL-BREF, DASH questionnaire results, as well as the IPAQ-short, the reported smoking status and the reported alcohol consumption results.

The implementation outcomes will be the number of participants entering the groups, the number of people following the entire intervention (attendance at 75% or more of the group meetings), and the cost of the intervention.

Randomisation will be applied automatically by Redcap©.

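### The 24-month smoking comparison makes no use of the smoking item recorded at screening: a valid test, but a less powerful one than the data already held would allow

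*Protocol article*

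**What the plan says.** All references are to the protocol article.

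- **Test.** Statistical methods: "The qualitative endpoints will be compared between the two groups using a Chi-square test". Quantitative outcomes get a Student test. Neither uses a baseline value.
- **Adjustment.** The same section adds: "Secondary, multivariate analyses will be performed using a linear model to adjust for potential confounding factors". No covariate is named, and these models stand outside the two-step confirmatory hierarchy.
- **Place of smoking.** Outcomes lists smoking among the 24-month secondary outcomes: "BMI reduction, smoking level, modification of self-declared alcohol consumption". Statistical methods tests six secondary endpoints with Holm-Bonferroni, in a demonstrative manner only if the primary comparison is significant.
- **Scale of smoking.** The wording varies. The Abstract says "smoking level will be assessed according to the NL-IHRS scoring system". Sample size speaks of "differences in scores for quality of life (WHOQUOL-BREF), DASH questionnaire, IPAQ-short, reported smoking status, reported alcohol consumption". The first can be an item score; the second reads more like a category.
- **Baseline.** In Stage 1, "screeners will canvass participants, assess the NL-IHRS and deliver the appropriate brief advice". Under Eligibility criteria, entry to the RCT requires a score of 9 to 15, so each randomised participant has a completed NL-IHRS. For the screened population, Statistical methods promises that "the frequency of the modifiable risk factors listed in the score will be described", so item-level data are kept.

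**The concern.** Smoking status tend to persist: most people who smoke, or do not smoke, at entry can be expected to be in the same state two years later. A comparison of 24-month smoking alone therefore carries a large component of variation that was fixed before randomisation and has nothing to do with the intervention. The trial holds the variable that would remove it, on the endpoint's own scale and measured before allocation, but the confirmatory test leaves it out. The planned linear model does not fill the gap: it is secondary, does not name baseline smoking, and is a poor fit if smoking is categorical.

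At stake is the chance of detecting a real effect on one of the behaviours that the article's Background lists as modifiable, in a family where the first Holm step is at 0.05/6.

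**Working it through.** **Inputs from the article (Statistical methods):** 394 per arm; alpha 0.05, taken as two-sided because sidedness is not stated; effect size 0.20; six secondary endpoints under Holm; stated power of about 68% for each. **Assumed, because the article gives none:** smoking prevalence at entry, quit rates, uptake among non-smokers, and the baseline-to-24-month correlation (rho).

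**1. The plan's own figures reproduce.** The expected z is 0.20 × √(394/2) = 2.807.
- At 0.05: Φ(2.807 − 1.960) = 80.2%.
- At 0.05/6: Φ(2.807 − 2.638) = 56.7%.
- Simulating six tests under Holm gives average power per endpoint of 68.6% if they are independent, and 67.1% at an inter-endpoint correlation of 0.5. This agrees with the stated 68%.

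The 0.05/6 figures below are for the strictest Holm step; the 68% averages over the whole stepwise procedure.

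**2. Adjustment at the plan's effect size.** Adjusting for baseline multiplies the residual SD by √(1 − rho²), so power = Φ(2.807/√(1 − rho²) − z). For rho = 0.5, 2.807/0.866 = 3.241.

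| rho | power at 0.05 | power at 0.05/6 |
|---|---|---|
| 0 (unadjusted) | 80.2% | 56.7% |
| 0.5 | 90.0% | 72.7% |
| 0.7 | 97.6% | 90.2% |
| 0.8 | 99.7% | 97.9% |

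**3. Smoking as a binary status.** Let b be the proportion smoking at entry, q the quit rate in an arm and u the uptake among non-smokers. Smoking at 24 months in that arm is p = b(1 − q) + (1 − b)u. Power = Φ[(difference − z × SE0)/SE1], where SE0 is the standard error under no difference and SE1 under the assumed difference.

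Example: b = 30%, quitting 10% v 20%, u = 1%.
- 24-month smoking: 0.3 × 0.9 + 0.7 × 0.01 = 27.7%, v 0.3 × 0.8 + 0.007 = 24.7%. The difference is 3.0 points.
- Unadjusted: SE0 = √(2 × 0.262 × 0.738/394) = 0.03133; SE1 = 0.03131. Power = Φ(−1.003) = 15.8% at 0.05.
- Stratified by entry smoking (Mantel-Haenszel): SE0 = √[(0.3 × 2 × 0.85 × 0.15 + 0.7 × 2 × 0.01 × 0.99)/394] = 0.01514; SE1 = √[(0.3 × (0.09 + 0.16) + 0.01386)/394] = 0.01502. Power = Φ(0.021) = 50.8% at 0.05.
- At 0.05/6: about 5% v 25%.

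The same formulas over the assumed range, with control quitting at 10%:

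| entry smokers | intervention quitting | uptake | 0.05: unadjusted → stratified | 0.05/6: unadjusted → stratified |
|---|---|---|---|---|
| 20% | 20% | 3% | 11% → 24% | 3% → 8% |
| 30% | 20% | 1% | 16% → 51% | 5% → 25% |
| 30% | 25% | 1% | 30% → 81% | 12% → 57% |
| 30% | 30% | 1% | 50% → 95% | 25% → 84% |
| 40% | 30% | 3% | 66% → 98% | 40% → 91% |

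Over 20-40% entry smokers, intervention quitting of 20-30% and uptake of 1-3%, the gain at 0.05 runs from about 14 points (first row) to about 50 (third row). Simulation of both tests agrees with these values.

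**4. Type I error.** With equal quit rates in the two arms, simulation gives a rejection rate of about 0.05 for both the Chi-square and the stratified test.

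**The case against.** **Most of the power is thrown away.** A reader might infer this from the 16% v 51% example. The documents do not support it. The only effect size they state is 0.20, and there the unadjusted test keeps 80.2/90.0 = 89% of the attainable power at 0.05 with rho 0.5, and still 80.2/99.7 = 80% with rho 0.8. The large relative losses belong to overall effects smaller than the one planned for: 27.7% v 24.7% is a standardised difference (Cohen's h) of about 0.07. In that example the adjusted test reaches only 51%, so a modest effect on quitting would still often be missed. On the other side, 0.20 is demanding for smoking: with 30% smokers at entry, 10% control quitting and 1% uptake it needs about 38% quitting in the intervention arm. The gain is therefore real, but its size is not fixed by the article.

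**Chance imbalance in entry smoking biases the result.** This does not stand. Random imbalance is already covered by the type I error, which both tests hold. Any correlation within the motivational groups is a separate matter that this adjustment does not address.

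**The Chi-square may not govern smoking.** This stands as far as it goes: the article does not say which endpoints are qualitative. It does not rescue the plan, because the Student test omits the baseline item in the same way.

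**Adjustment is left to an analysis plan that is not shown.** Covariate lists often are. Here, however, the article fixes unadjusted tests for the comparisons and labels the adjusted models secondary.

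**The consequence is limited.** True: smoking is one of six secondary endpoints and is tested confirmatorily only after a significant primary result.

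**Conclusion.** The point holds as one of efficiency. The Holm-tested smoking comparison leaves out a pre-randomisation measurement of the same item that the trial already holds for every participant, and the secondary linear model does not make up for it. The test remains valid.

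The gain from adjustment is 10 points at 0.05 and 16 points at 0.05/6 at the plan's effect size of 0.20, if rho is 0.5. It is about 14 to 50 points at 0.05 under the assumed smoking scenarios. Prevalence, quit rates, uptake and correlation are all assumptions; adjustment raised power in every scenario tried, but its size cannot be derived from the article. Neither a loss of most of the power nor a bias can be claimed.

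**What to change.** In Statistical methods:

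1. State whether 24-month smoking is analysed as a category or as an item score.
2. Make the confirmatory comparison baseline-adjusted, in the same place in the Holm family. For a category, use a Mantel-Haenszel test stratified by the screening smoking category, or a logistic or ordinal model with arm and that category. For a score, use ANCOVA on the screening item.
3. Keep the unadjusted test as a sensitivity analysis.
4. If an odds ratio from a model is reported, note that it is conditional on baseline smoking, and give a stratified risk difference beside it.

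The cost is a sentence or two. No new data, visits or participants are needed; the screening record only has to be linked to the trial record, which checking eligibility on the score requires in any case. The change should be made before outcome data by arm are seen.
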